## Abstract

**Background:**

Chronic migraine is frequently refractory to available preventive therapies. Image-guided cryoneurolysis of the greater occipital nerve (CryoGON) may provide longer-lasting relief than conventional greater occipital nerve (GON) blocks. This Stage 1 Registered Report describes a prospective, exploratory study evaluating whether response to a conventional GON block predicts subsequent response to CryoGON, and assesses open-label safety, tolerability, feasibility and efficacy of CryoGON.

**Discussion:**

This study will provide the first systematic evaluation of whether a simple, widely available GON block can guide patient selection for CryoGON and will generate foundational open-label data on its clinical performance and safety. Findings will inform the design and justification of a subsequent sham-controlled trial.

**Trial registration and approvals:**

The study will preregister at
ClinicalTrials.gov. and obtain all necessary ethical approvals before study initiation.

Sponsor: St. Olav’s University Hospital, Trondheim, Norway.

Funding: Stiftelsen Dam (grant SDAM_FOR701626).

## Introduction

Migraine is a disabling primary headache disorder with a lifetime prevalence of 17% of the population and ranking as the second leading cause of disability in females under 50 years of age.
^
1
^ Chronic migraine, defined by ≥15 headache days per month for >3 months with ≥8 migraine days, affects 1.4–2.2% of the population and imposes a major personal and socioeconomic burden.
^
2
^ Current preventive treatments include repurposed oral drugs and botulinum toxin A, as well as treatments targeting the CGRP neuropeptide system, yet many patients remain insufficiently treated. Suitable treatment options for woman of childbearing potential not using highly effective contraception, pregnant and nursing woman are even more limited. Indeed, chronic migraine and related complications, such as medication overuse headache causes women of childbearing potential (WOCBP) to avoid childbearing or to having fewer children then intended,
^
3
^ underscoring the need for novel non-pharmacological treatment strategies.

Greater occipital nerve (GON) block with a local anaesthetic is widely used as a transitional or rescue therapy in migraine and trigemino-autonomic cephalalgias.
^
4
^ A recent randomised trial and a meta-analysis support modest efficacy in chronic migraine, with reductions in headache days and responder rates superior to placebo.
^
5
^ However, short duration of effect and the need for repeated injections limit its preventive utility.

The analgesic effects of GON blocks on headache disorders, often characterized by pain in trigeminal regions, suggest a functional interaction between the occipital and trigeminal systems. The functional overlap between occipital and trigeminal sensory processing takes place at the level of the upper cervical spinal cord where nociceptive fibres from both regions converge on the trigeminocervical complex (
Figure 1). This functional and anatomical coupling is demonstrated in several animal studies.
^
6–
10
^ In humans, when the greater occipital nerve (GON) is pharmacologically blocked in participants without a headache diagnosis or other pain condition, a reduced nociceptive trigeminal response was observed compared to placebo.
^
11
^ Similar studies have not been performed in headache sufferers.

**Figure 1. f1:**
[figure not shown]
Lateral view of the left side of the head illustrating the trigeminal (red) and occipital (blue) nerves. Together, these nerves provide sensory innervation to the entire head and are functionally coupled within the trigeminocervical complex (TCC). A needle illustration indicates the approximate segment of the greater occipital nerve targeted by conventional GON blocks and by the CryoGON procedure. Bilateral treatment (not shown) is performed for both interventions.

Cryoneurolysis is an established treatment in pain medicine.
^
12
^ By applying cold temperatures to neural structures, it induces reversible Wallerian degeneration (axonotmesis) with subsequent regeneration, resulting in a long-acting but reversible nerve block. Cryoneurolysis has demonstrated efficacy in trigeminal and occipital neuralgia, with reported pain relief lasting several months.
^
13–
16
^ A sham-controlled study in cervicogenic headache, in which the control-arm received GON-block with steroids, did not demonstrate a statistically significant between-group effect. The investigators in this trial used anatomical landmarks and nerve stimulation to guide the cryoprobe, and insufficient targeting could have reduced the efficacy in the cryoneurolysis arm. It is to date no published reports on efficacy or safety in primary headache conditions to our knowledge, but cryoneurolysis towards the GON is currently studied in an open label pilot study in chronic migraine (NCT06554886).

Surgical navigation systems enable accurate percutaneous targeting of deep neural structures using pre-procedural imaging and real-time tracking. Applied to the GON, navigation-guided cryoneurolysis (CryoGON) offers a minimally invasive, office-based procedure with the potential to provide longer-lasting preventive benefit than conventional GON blocks.

This trial is designed to determine whether response to a conventional GON block predicts subsequent response to CryoGON in chronic migraine, thereby assessing the clinical utility of the block as a decision tool. Secondary objectives include evaluation of open-label efficacy, safety, tolerability, and feasibility of the CryoGON procedure. To that end, this trial will inform the design of future studies by assessing the feasibility and rational for conducting a sham-controlled trial.

### Study objectives

Primary objective

To evaluate whether clinical response to a conventional greater occipital nerve (GON) block is associated with treatment response to navigation-guided cryoneurolysis of the GON (CryoGON) in patients with chronic migraine.

Secondary objective

To evaluate the open label clinical performance of CryoGON as a potential new treatment for chronic migraine.

### Timeline

The study is planned to be initiated in 2026 with a duration of recruitment for 2 years ending in 2028. Data lock is thus planned in 2028 and submission of the stage 2 manuscript by end of 2028 or start of 2029. Publication will adhere to the Vancouver guidelines. We do not intend to use professional writers.

## Methods

This protocol publication is based on the clinical investigation plan (study protocol), version 1.0, dated 14th of October 2025. This will be a clinical investigation of a medical device for cryoneurolysis, that will be conducted in accordance with the Declaration of Helsinki, Norwegian law (including the Medical Device Regulation), and ISO 14155:2020 (Clinical investigation of medical devices for human subjects – Good clinical practice). The trial will be initiated following approval by the competent authorities, the Regional Committee for Medical and Health Research Ethics and institutional approval by the sponsor. The inclusion and data collection of each study participant will commence only after their written informed consent has been obtained. Amendments to the protocol will be implemented only after appropriate review and approval by the relevant parties. The study will be prospectively registered at
ClinicalTrials.gov prior to enrolment of the first participant. All items from the WHO Trial Registration Data Set will be included in the
ClinicalTrials.gov record and correspond to the information provided in this protocol publication.

The study is investigator-initiated and will be sponsored by a public hospital (St Olav’s university hospital, 7006 Trondheim, Norway,
[contact]). It will be conducted under the auspices of the Norwegian Headache Research Center (NorHead), a publicly funded academic center at the Norwegian University of Science and Technology. Funding for this study will be provided by the DAM Foundation (Stiftelsen Dam, grant no SDAM_FOR701626), a Norwegian non-profit foundation that allocates research grants from the surplus of the national lottery operator (Norsk Tipping). The grant application was submitted in collaboration with the national patient organization
*Hodepine Norge (eng. Headache Norway)*, which also coordinates patient involvement in the design and conduct of the study. A prerequisite of the DAM Foundation grant award is that dissemination follows the two-stage Registered Report publication format.

The funding body, sponsor or any other party than the authors of this paper, had no role in the study design, in writing the clinical investigation plan (study protocol) and the decision to submit the protocol for publication.

Participants are insured through the Norwegian System of Patient Injury Compensation (Norsk pasientskadeerstatning). No post-trial care is provided with-in the framework of the trial.

### Study design

The trial will be conducted as a single-site, open-label study within the Norwegian public healthcare system, which reimburses patient travel and accommodation expenses. Should any co-payment be required, these costs will be covered by the study. No remuneration or financial incentives will be offered beyond reimbursement of necessary expenses. The study will be designed and conducted according to the guidelines of the International Headache Society.
^
17
^

Study recruitment

Recruitment will be facilitated through the NorHead national research infrastructure. Once enrolment opens, study information will be made available on governmental and institutional websites as well as through social media platforms. Patients may be referred by their treating physician or may self-register via the NorHead online portal. Study personnel will perform pre-screening of candidates, and only patients considered potentially eligible will be scheduled for a formal eligibility assessment by a neurologist.

Eligibility criteria

Inclusion and exclusion criteria are summarized in
Table 1. In brief, eligible participants will be adults (≥18 years) with chronic migraine, with or without aura, fulfilling the International Classification of Headache Disorders (ICHD-3) criteria and verified by a neurologist at inclusion. Participants must have a history of chronic migraine for at least one year, with onset of episodic migraine before age 50 and onset of chronic migraine before age 65. Preventive medications must have been stable for at least three months (or ≥5 half-lives, whichever is longer) prior to screening, and participants must agree to maintain their regimen throughout the study. Individuals treated with onabotulinumtoxinA must have received at least three consecutive PREEMPT-protocol injection cycles with stable intervals. Only patients deemed suitable for both a conventional GON block and CryoGON by the investigator, and capable of providing written informed consent, will be enrolled.

**Table 1. T1:** inclusion and exclusion criteria.

Inclusion criteria	Exclusion criteria
1. Participant must be 18 years at the time of signing the informed consent. 2. Migraine, with or without aura, fulfilling the International Classification of Headache Disorders (ICHD) III criteria 1.3. for chronic migraine at time of inclusion, verified by a neurologist. 3. Chronic migraine at least for a period of 1 year prior to inclusion. 4. Debut of episodic migraine before the age of 50, and chronic migraine before the age of 65. 5. Subject has had no change in type, dosage or dose frequency of preventive headache medications <3 months prior to inclusion, or a minimum of 5 half-lives, whichever is longer. In the case of treatment with botulinumtoxin A following the PREEMPT injection regimen, a minimum of three consecutive treatments with equal between-treatment intervals are required. 6. Subject agrees to maintain current preventive headache medication regimens (no change in type, frequency, or dose) during baseline until 12 weeks following CryoGON-treatment. 7. Be an appropriate candidate for the study interventions required in this study on the basis of the clinical judgment of the investigator. 8. Capable of giving signed informed consent which includes compliance with the requirements and restrictions listed in the informed consent form (ICF) and in the study protocol.	1. Subject been treated with injections targeting the greater occipital nerve or the Occipital/suboccipital region, except for onabotulinumtoxin treatment in accordance to the PREEMT injection regime the last 12 weeks prior to baseline, or during the baseline period. 2. Subject is unable to differentiate a migraine day from other concomitant headache disorders. 3. Subject with secondary headache conditions, with the exception of medication overuse headache. 4. Subject with occipital neuralgia or neuropathy, or that otherwise exhibit disturbed sensory function in the innervation area of the GON that in the opinion of the investigator can disturb the evaluation of CryoGON procedure success. 5. Subject has had a change in type, dosage or dose frequency of preventive headache medications during the baseline period. 6. Subject is or has been treated with occipital nerve stimulation. 7. Ongoing abuse of drugs (including narcotics) or alcohol. 8. More than 4 days of opioid use per month (including codeine and tramadol), and any use of barbiturates. 9. Other pain conditions, not intended to be treated in this study, that in the opinion of the investigator could interfere with study procedures, accurate pain reporting, and/or confound evaluation of study endpoints. 10. High probability of deterioration due to other medical conditions, that in the opinion of the investigator may confound outcome assessment. 11. Patients with comorbid psychiatric disorders with psychotic or other symptoms making compliance with the study protocol difficult, at the discretion of the investigator. 12. Other coexisting current medical conditions, including, but not limited to, bleeding diathesis, cryopathies (cryoglobulinemia, paroxysmal cold hemoplobinuria), and thrombophilia, that presents excess procedural risk, in the opinion of the investigator. 13. Abnormal pain behavior, inappropriate medication use and/or unresolved psychiatric illness, that in the opinion of the investigator are significant enough to impact perception of pain, compliance with intervention and/or ability to evaluate treatment outcome. 14. Anomaly or trauma which renders the planned procedure difficult. 15. Subject currently has an active abscess or a local infection at the site of intervention based on present symptoms. 16. Subject has been diagnosed with any major infectious processes such as osteomyelitis, or primary or secondary malignancies involving skull or site of intervention that have been active or required treatment in the past 6 months. 17. Current participation in another treatment study.

Key exclusion criteria include prior GON-targeted injections within 12 weeks of baseline, inability to differentiate migraine days from other headache types, or coexisting secondary headache disorders (except medication overuse headache). Patients with occipital neuralgia or neuropathy or other pain conditions that may confound evaluation of study outcomes will be excluded. Additional exclusions include unstable preventive medication regimens, prior or current occipital nerve stimulation, frequent opioid or any barbiturate use, significant psychiatric comorbidity or abnormal pain behaviour, relevant medical conditions increasing procedural risk (e.g. bleeding diathesis), and ongoing treatment site infection.

Study outline

The study will comprise four in-clinic visits and a series of structured follow-up contacts, separated by observation periods with prospective daily eDiary data collection (
Figure 2). At visit 1, eligibility will be assessed and written informed consent obtained via an electronic signature in a secure institutional digital platform (the eFORSK platform). Eligible participants will then enter a minimum 28-day baseline period, which serves both as a screening phase and to establish baseline data for endpoint assessments. A diary adherence of at least 90% (≥25 of 28 days) will be required to proceed. At visit 2, participants will be re-screened, and those meeting criteria will receive bilateral conventional greater occipital nerve (GON) blocks followed by a minimum 28-day observation period. A structured telephone call will be conducted one week after the procedure to capture any treatment-emergent adverse events and confirm scheduling for visit 3. At visit 3, eligibility will again be reassessed, including review of contraindications to CryoGON, confirmation of ≥90% diary adherence, and stable prophylactic regimens. Participants meeting criteria will undergo the CryoGON procedure (navigation-guided cryoneurolysis of the GON). Structured telephone follow-ups will be performed at weeks 1, 4, and 8, and a final in-clinic assessment will be conducted at week 12 post-CryoGON.

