Technical success	Technical success is a composite (i) surgeon-confirmed completion of planned lesion at intended target with no device deficiency; (ii) Participant-reported numbness lasting >72 hours within the expected bilateral GON sensory distribution.
Device deficiency	Defined according to MDR (EU 2017/745) Art. 2(59) as any inadequacy of the medical devices used during the CryoGON procedure with respect to its identity, quality. durability, reliability, usability, safety or performance, and includes malfunctions, user errors and inadequacy in the information supplied by the manufacturer including labelling.
Procedure time	Elapsed time, measured in whole minutes, from the moment the participant enters the procedure room until the moment the participant leaves the room following completion of the CryoGON intervention.
Diary adherence	Proportion of days with completed eDiary entries per 28 day period.

GON = Greater occipital nerve, CryoGON = Cryoneurolysis of the GON, AE = Adverse event, SAE = Serious AE, ADE = Adverse device effect, SADE = Serious ADE, MDR = Medical device regulation.

**Table 4. T4:** Overview of study endpoints.

Objective	Outcome measure	Endpoint definition	Time point

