**Secondary feasibility endpoints**			
Evaluate the number of device deficiencies	Device deficiencies	Incidence of device deficiencies affecting the planned procedure (classified by type); per-procedure proportion with ≥1 deficiency.	Procedure day
Evaluate the diary adherence	Number of days of scheduled eDiary days with valid entries	Percentage of scheduled eDiary days with valid entries per period 28 day period; threshold ≥90% considered acceptable.	Week 1-4 post-cGON; Weeks 1–4, 5–8, 9–12 post-CryoGON
Evaluate procedure time	Procedure time in minutes from procedure initiation until completion	The average procedure time.	Procedure day

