### Protocol violations

Protocol violations in this study are headache diary nonadherence defined as <90% adherence and/or alterations in headache preventive treatment during trial participation. Electronic headache diary adherence will be calculated at 4-week (28 days) intervals.

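### The baseline diary gate equates at least 90% adherence with 25 of 28 days, but 25/28 is 89.3%, so the gate contradicts itself and the protocol-violation rule for a participant with exactly 25 days

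*Protocol article*

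**What the plan says.** In the Study outline text under Study design, consented participants start a diary run-in: "Eligible participants will then enter a minimum 28-day baseline period". The condition for moving on to the GON block is "A diary adherence of at least 90% (≥25 of 28 days) will be required to proceed". At visit 3, before CryoGON, the same text asks for "confirmation of ≥90% diary adherence, and stable prophylactic regimens", with no day count.

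Table 3 defines diary adherence as "Proportion of days with completed eDiary entries per 28 day period". The section Protocol violations counts as a violation "headache diary nonadherence defined as <90% adherence and/or alterations in headache preventive treatment during trial participation", and adds: "Electronic headache diary adherence will be calculated at 4-week (28 days) intervals". The Statistical analysis section restricts the per protocol set (PPS) to participants without violations. It uses the full analysis set (FAS), everyone who received CryoGON, for the main analysis. Under Sensitivity analyses, the PPS supports one of the additional analyses, while the key sensitivity analysis uses the technical success set.

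Table 4 lists diary adherence as a secondary feasibility endpoint, "threshold ≥90% considered acceptable", for weeks 1–4 after the GON block and the three 4-week windows after CryoGON.

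**The concern.** The gate gives a percentage and a day count as if they were the same rule. They are not, and they disagree on the one count, 25 days, that the sentence names as its limit. Two members of staff could admit and refuse the same participant, each with support in the text, and an automated check needs a single number.

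The percentage recurs in the violation rule. A participant admitted on the day count can therefore hold a violation before any treatment is given and be left out of the per protocol analysis despite meeting the stated entry requirement. The protocol itself calls adequate adherence essential for valid headache-day endpoints, so the threshold should be unambiguous.

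**Working it through.** **Inputs.** Window length 28 days and threshold 90% (Study outline, Table 3, Protocol violations); stated equivalent 25 days (Study outline).

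**The plan's own figure.** 0.90 × 28 = 25.2. Rounding to the nearest whole day gives 25, which is the likely origin of the parenthesis. A rule of at least 90% needs the next whole number up, which is 26.

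**Adherence by day count.**

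| Completed days | Share of 28 | At least 90%? | Meets the 25-day count? |
|---|---|---|---|
| 24 | 85.7% | no | no |
| 25 | 89.3% | no | yes |
| 26 | 92.9% | yes | yes |
| 27 | 96.4% | yes | yes |
| 28 | 100% | yes | yes |

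Only 25 days is classified differently. Rounding the percentage does not help, since 89.3% rounds to 89%. The protocol states no rounding rule.

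**The rules side by side for a 25-day diary.**

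- Baseline gate by day count: pass.
- Baseline gate by percentage: fail.
- Violation rule, if it covers baseline: violation, hence not in the PPS.
- Visit 3 gate, violation rule in later windows, and Table 4 threshold: below 90% in each. These agree with one another, because none of them carries a day count.

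**How often it could matter.** The protocol gives no completion rate, so this is an illustration. It assumes that each day is completed independently with probability p. Then P(exactly 25 of 28) = C(28,3) × p^25 × (1−p)^3, with C(28,3) = 3276.

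- p = 0.97: 3276 × 0.97^25 × 0.03^3 = 4.1%
- p = 0.95: 3276 × 0.95^25 × 0.05^3 = 11.4%
- p = 0.90: 3276 × 0.90^25 × 0.10^3 = 23.5%

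The share passing the gate under each reading differs by exactly these amounts:

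| p | 25 days or more | 26 days or more |
|---|---|---|
| 0.97 | 99.1% | 94.9% |
| 0.95 | 95.1% | 83.7% |
| 0.90 | 69.5% | 45.9% |

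**The case against.** The strongest reply is that this is a one-day rounding slip in one parenthesis with little statistical consequence. Much of that stands. The primary and key secondary analyses use the FAS, whose membership after treatment does not depend on diary adherence. The PPS serves only an additional sensitivity analysis. The eDiary accepts entries for the current day and the two days before, and investigators monitor adherence on a dashboard. Both work against missed days.

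A reader might also infer more than the text supports, in three ways:

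- That the conflict exists in every 28-day window. It does not. After baseline the rules use 90% without a day count and agree. The problem would spread to visit 3 or later windows only if staff carried the 25-day equivalence forward.
- That a 25-day baseline diary counts against the feasibility result. Table 4 lists no baseline time point for that endpoint.
- That exclusion from the PPS is certain. The violation definition mentions trial participation without saying whether baseline belongs to it. Inclusion is the more natural reading, since baseline follows consent, supplies endpoint data and is nowhere exempted. It is still a reading.

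What the reply does not remove is that the document states two numbers for one eligibility rule and they disagree. That is not detail left to the analysis plan.

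**Conclusion.** The point holds for the baseline window. As written, the gate both admits and refuses a participant with exactly 25 completed days. On the reading that trial participation includes baseline, the same diary is also a protocol violation that removes the participant from the PPS. The arithmetic needs no assumption.

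The effect is modest: one day count, one window, entry to the GON block, and one secondary sensitivity analysis. The gate influences who can reach the FAS but does not alter FAS membership after treatment. The share of participants affected, about 4% to 24% for daily completion between 97% and 90%, rests on assumed rates and on independence between days. Missed days may well cluster, so the range shows only that the case need not be rare. The correction is worth making before enrolment because it concerns a rule that staff must apply to each participant.

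**What to change.** Preferred: change the parenthesis in the Study outline text to ≥26 of 28 days. This matches the 90% used at visit 3, under Protocol violations and in Table 4, and nothing else needs to change. The cost is some additional screen failures, equal to the share of participants with exactly 25 days. That is small if completion is high and larger if it is not.

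Alternative, if 25 days is what the sponsor intends: lower the percentage to one that 25 of 28 meets, such as ≥89%. Use it in both gates of the Study outline, under Protocol violations (nonadherence then being 24 days or fewer of 28) and in Table 4. This avoids the extra screen failures. It also slightly relaxes the visit 3 gate, the per protocol definition and the feasibility threshold, and the protocol should say so.

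In either case, state the threshold in days, add one clause saying whether the violation rule covers the baseline period, and set the diary dashboard or eCRF check to the same number. The cost is wording and one edit check.
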